#### Secondary Outcomes

##### Overview

The secondary outcome is the effect of the intervention on peak exercise capacity, handgrip strength, independence, and quality of life. Peak exercise capacity and strength parameters were chosen because they are important factors for improving quality of life [11,15] and independence [10,14]. Quality of life and independence were chosen because these parameters are integral to the overall rehabilitation goal of people with SCI [50]. Furthermore, the guidelines for the conduct of clinical trials for SCI [51] suggest using the Spinal Cord Independence Measure III (SCIM III) for functional assessments and the Short Form–36 Health Survey (SF-36) for quality-of-life assessments.

##### Ramp Exercise Test

Participants will perform a ramp exercise test on an arm crank ergometer (ergo-metrics 800s, Ergoline). The rotational axis of the ergometer will be set at shoulder level. The distance between the wheelchair and ergometer will be set such that there is a slight flexion in the elbow joint when the participant extends their arm. A 3-minute warm-up will be conducted at a cadence of 60 to 70 revolutions per minute and a resistance of 0 W. After the warm-up, the workload will be increased by 10 W per minute (1 W every 6 seconds) until volitional exertion is reached [52]. Volitional exertion is reached when the cadence drops below 50 revolutions per minute [52] or rate of perceived exertion exceeds 18 on the Borg scale ranging from 6 to 20 [53]. Heart rate (Polar H7 chest belt, Polar Electro Oy), workload, and respiratory gas exchange parameters (MetaMax 3B, Cortex) will be monitored throughout the exercise test [52]. Participants will be asked to rate their level of perceived exertion on the Borg Rate of Perceived Exertion scale upon the termination of the exercise test.

##### Handgrip Strength

The determination of handgrip strength using a handgrip dynamometer is a widely applied, simple, and reliable method for evaluating the efficacy of a treatment [54] and predicts functional independence [55]. An electronic hand dynamometer (Trailite TL-LSC1000, LiteXpress GmbH) will be used to determine maximal handgrip strength. Participants will be asked to grip the handle with maximal effort [56]. As warm-up trials decrease the variability of strength measurements [54], participants will be given 1 warm-up trial for each hand. A total of 3 attempts will be made for each hand for a duration of 3 seconds each at a 90-degrees elbow flexion and neutral wrist position [54,55,57]. A rest period of 60 seconds will be provided in between. The sum of the highest values for the right and left hands will be used to determine handgrip strength [55].

##### Independence

The SCIM III was developed to sensitively detect changes in function (eg, concerning respiration) in individuals with SCI [58] and changes in various activities of daily living (eg, bed-wheelchair transfers) [59]. It shows a very high interrater reliability (*r*=0.98; *P*<.001). The SCIM III is subdivided into 3 categories: (1) self-care, (2) respiration and sphincter management, and (3) mobility. The score ranges from 0 to 100. A higher score indicates greater independence. In this study, the German version of the SCIM III will be used [60].

##### Quality of Life

The SF-36 is the most commonly used questionnaire to assess quality of life in people with SCI and has been shown to be valid and reliable for this population [61]. The survey comprises 36 items across 8 domains. The score ranges from 0 to 100, with a higher score indicating a better quality of life [62]. As previously recommended [11,63,64], 2 items referring to “climbing stairs” were replaced with “going up stairs” (German: *Stufen überwinden*), and 3 items referring to “walking” were replaced with “going” (German: *fortbewegen*).

### Data Management and Analyses

#### Data Management

Data will be entered into Microsoft Excel (version 2018) by one researcher and double-checked by another researcher before being analyzed using SPSS Statistics (version 29, IBM Corp). To ensure confidentiality, data will be recorded using the participants’ study ID instead of their names. All data forms will be stored electronically and protected by a password in addition to being stored in paper form and secured in a locker in a room with restricted access. Only the authors of this manuscript will have access to the full data set. The principal investigator (JB) will monitor AEs. The data will be deleted upon participants’ request.

#### Sample Size

The aim is to recruit a total of 45 participants between November 2022 and January 2023: 30 participants at the GSU and 15 participants at the BG clinic Tübingen. As this is a pilot trial, the sample size was based on previous studies with similar aims and methods [27,28] and recommendations for usability testing [65].

#### Qualitative Analysis

The interview audio recordings will be transcribed verbatim and analyzed using a qualitative content analysis approach according to Mayring [66] using MAXQDA (version 22, VERBI). Categories arising from the interview guide will be determined a priori. Two researchers will identify codes for the first 3 interviews and assign them to a category deductively. An inductive approach will be used to create additional categories and subcategories. Disagreements between researchers during the categorization process will be discussed until a consensus is reached. The interviews will be revised upon considering possible changes in the category system. More interviews will be analyzed until data saturation is achieved [40,45].

#### Quantitative Analysis

Quantitative data analysis will be performed using SPSS. All data will be tested for normal distribution using the Shapiro-Wilk test. Study participant characteristics will be presented descriptively by calculating means and SDs for normally distributed variables. Median values and IQR will be calculated for skewed continuous variables, and absolute and relative frequencies will be calculated for nominal variables. Group differences at baseline will be calculated for independent samples using a 2-tailed *t* test, Mann-Whitney *U* test, or chi-square test depending on the distribution and level of measurement. At t_1_, normally distributed continuous variables will be analyzed using a mixed analysis of variance model to test for significant effects for group and time. For skewed continuous variables, Wilcoxon and Mann-Whitney *U* tests will be conducted to test the differences between the groups and between t_0_ and t_1_. The significance level will be set at *P*<.05. Absolute and relative frequencies will be reported for adherence and retention.

Feasibility will be assumed if (1) at least 66% of the training sessions (equivalent to 2 out of 3 sessions per week) are completed [43] and (2) the retention rate is at least 75% [67]. Exercise diaries will be analyzed in terms of the frequency, duration, and intensity of the training sessions. Safety will be assessed by comparing the number of study-related AEs or SAEs in the intervention group with that in the waitlist control group [68].

Spearman correlations will be used to assess the association between performance and strength outcomes and SCIM III and SF-36 outcomes. Subgroup analyses might be conducted for lesion level (high vs low paraplegia) and age. Missing data will not be imputed.

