### Study Design

This pilot mixed methods block-randomized controlled feasibility trial with an allocation ratio of 1:1 for the intervention and waitlist control groups is conducted at the German Sport University Cologne (GSU), Germany. The trial was registered with the German Clinical Trials Register (DRKS00030370).

Participants will be recruited at the GSU and the SCI center at the BG (*Berufsgenossenschaft*; English: occupational insurance association) clinic Tübingen, Germany. Participants will be recruited at the GSU via the project newsletter, the project website, social media, and by contacting rehabilitation centers and spinal cord associations. The BG clinic in Tübingen will recruit among their patients.

Measurements will be conducted at baseline (t_0_) and after the intervention (t_1_; Table 1). The primary outcomes (feasibility, usability, and safety) will be assessed during the intervention and at t_1_. The secondary outcomes (peak exercise capacity, handgrip strength, independence, and quality of life) will be assessed at t_0_ and t_1_. As data collection at the BG clinic Tübingen will focus on the primary outcomes and owing to limited capacity, the ramp exercise test for evaluating peak exercise capacity and handgrip strength test will be conducted only at the GSU and not at the BG clinic Tübingen. After randomization and group allocation, participants in the intervention group will be provided with the ParaGym mobile exercise app and uptake a 6-week home-based training intervention. The participants will be instructed to complete 3 training sessions per week. For this cohort, resistance training for at least 2 days a week is recommended [2,6]. As the training sessions delivered by the app comprise not only strength but also aerobic and flexibility exercises, we decided to provide training sessions for 3 days instead of 2. Eitivipart et al [34] recommend 3 sessions for a minimum duration of 20 minutes per week over at least 6 weeks to achieve substantial outcomes. The waitlist control group will proceed with their usual care and receive access to the mobile app once they have completed the trial. After the 6-week intervention, participants in the intervention group will be interviewed over the phone to assess feasibility and usability. Subsequently, both groups will return to the study site (t_1_) for the SUS questionnaire and secondary outcome measures. The study design and planned participant flow are presented in Figure 3.

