#### Randomization

Only the 30 participants recruited at the GSU will be block randomized, stratified by the level (high vs low paraplegia) and completeness (complete vs incomplete paraplegia) of the SCI with a block size of 4. This will be done using Excel (Microsoft Corp). The randomization code will be released after the participant has completed all baseline measures. The randomization list will be password protected. Only JB and AL, who conduct the randomization and allocation, will have access to the list. No randomization is required at the BG clinic Tübingen, as data collection at that site focuses on the primary outcomes.

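### The plan tests baseline differences between randomised arms for significance; at 15 per arm these P values cannot show comparability, and adjustment for the t0 value would serve better (minor, secondary outcomes only).

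*Protocol article*

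**What the plan says.** In the Protocol article, Quantitative Analysis, participant characteristics are first to be summarised descriptively. A separate sentence then adds tests: "Group differences at baseline will be calculated for independent samples using a 2-tailed" t test, a Mann-Whitney U test or a chi-square test, according to distribution and measurement level. The threshold is general: "The significance level will be set at *P*<.05". No purpose is given for the baseline tests, and nothing follows from their result.

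The Randomization section says "Only the 30 participants recruited at the GSU will be block randomized", stratified by lesion level and completeness in blocks of 4, and "The randomization code will be released after the participant has completed all baseline measures". For the second site it says "No randomization is required at the BG clinic Tübingen". Study Design gives an "allocation ratio of 1:1 for the intervention and waitlist control groups", and Sample Size gives "30 participants at the GSU and 15 participants at the BG clinic Tübingen".

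For the effect analysis, Quantitative Analysis plans a mixed analysis of variance with group and time for normally distributed outcomes, and Wilcoxon and Mann-Whitney U tests for skewed ones. It names no covariate.

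**The concern.** A significance test asks whether a difference could have arisen by chance. When the arms are formed by randomisation after baseline is measured, the answer is known beforehand: it did arise by chance. The test therefore tells the reader nothing about the arms. What matters is how large an imbalance is and how strongly that variable predicts the outcome, and a P value measures neither.

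Two misreadings are at stake. A P below .05 may be taken as a sign that randomisation failed. A P above .05 may be taken as a sign that the arms are alike. The second is the more awkward in a trial with about 15 per arm, because imbalances large enough to move a between-group comparison will usually not reach significance. For lesion level and completeness the tests add nothing further, since stratification already controls them.

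**Working it through.** **Inputs from the protocol.** 30 randomised at GSU and 15 non-randomised at Tübingen (30 + 15 = 45); 1:1 allocation, so nominally 30/2 = 15 per arm; threshold P<.05. Table 1 has 5 rows of participant characteristics and 8 effectiveness rows measured at baseline, 13 in all. That count is mine; the protocol does not list the variables to be tested. It gives no power or error figure for these tests, so there is none to reproduce.

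**Assumptions.** Correlations between baseline variables 0 to 0.7; t0-t1 correlation (ρ) 0.7, with a range of 0.5 to 0.9; equal SDs at t0 and t1.

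**1. False flags.** Each test flags 5%. For at least one flag among k independent tests, the chance is 1 − 0.95^k:
- k = 11 (13 rows less the two stratification factors): 43.1%
- k = 13: 48.7%
- k = 16: 56.0%
- k = 22 (questionnaire domains counted separately): 67.6%

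Simulated t tests at 15 versus 15, with equally correlated variables, lower this. For k = 13 the chance is 43%, 34% and 25% at pairwise correlations of 0.3, 0.5 and 0.7. A fair overall range is about 25% to 68%.

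**2. What escapes the test.** The standard error of a standardised difference is √(2/15) = 0.365.
- An observed 0.5 SD difference gives t = 0.5/0.365 = 1.37 on 28 df, P = 0.18.
- The smallest observed difference reaching P<.05 is t(.975, 28) × 0.365 = 2.048 × 0.365 = 0.75 SD.
- By chance, an absolute difference above 0.5 SD occurs in 18.2% of randomisations per variable. In 18.2% − 5.0% = 13.2% it lies between 0.5 and 0.75 SD and is not flagged.

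**3. What an unflagged imbalance does at t1.** Take a realised 0.5 SD imbalance in the outcome itself, with ρ = 0.7:
- comparison of t1 values only (one way to apply the Mann-Whitney test): expected shift ρ × 0.5 = 0.35 SD
- comparison of change (the group-by-time contrast of the mixed model): expected shift (ρ − 1) × 0.5 = −0.15 SD
- comparison adjusted for the t0 value: expected shift 0 under a linear relation

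**4. Error rates.** In 100,000 simulated null trials at each ρ of 0.5, 0.7 and 0.9, the false-positive rate among trials with an unflagged 0.5 to 0.75 SD imbalance was 9-13% for the t1-only comparison and 6-9% for the change comparison. Over all trials both stayed at about 5%.

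**5. If Tübingen participants join one group (30 versus 15).** Real differences between the groups are then possible. The test would flag a true 0.5 SD difference 34% of the time and miss it 66% of the time.

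**The case against.** The strongest reply is that the tests do no work in the plan. They select no covariate, gate no analysis and declare no comparability. A descriptive summary is planned anyway, and Table 3 shows characteristics without P values. This stands: misreading of the P values is a foreseeable use, not a stated one.

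Second, a reader might infer that a given chance difference will be flagged about half the time. It will not. Each test flags 5%; the 49% is the chance of at least one flag among 13 independent tests. The protocol does not fix that count, and measures such as VO2 peak and peak power are unlikely to be independent.

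Third, a reader might infer that the planned effectiveness analysis is biased by 0.35 SD. The protocol does not support that. The figure applies to a comparison of t1 values alone and is conditional on a realised 0.5 SD imbalance. For normally distributed outcomes the mixed model uses both time points; its group-by-time contrast shifts less and in the opposite direction, although the text does not name the interaction. Averaged over randomisations there is no bias.

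Fourth, the statement that any significant result is a chance finding presumes sound allocation and a GSU-only comparison. Quantitative Analysis does not restrict the tests to GSU. If the non-randomised Tübingen participants enter a group, baseline differences need not be chance alone. The tests would then address a genuine question, but step 5 shows how poorly they answer it.

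Finally, handling of small expected counts in chi-square tests and similar detail may sit in an analysis plan not shown here, and I do not press it. The baseline tests and the effect model are stated choices, so they are open to comment.

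**Conclusion.** The point holds in a limited form. The protocol plans significance tests that, for the randomised GSU arms, cannot inform comparability. About 13 independent variables would give at least one spurious flag in about 49% of trials (roughly 25% to 68% over plausible counts and correlations), while observed imbalances below about 0.75 SD at 15 per arm would not be flagged.

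The consequence is misleading alarm or reassurance, together with an effect analysis that does not adjust for the t0 value. It is not an inflated overall error rate, and it is not evidence that randomisation is flawed. The shifts of 0.35 SD and −0.15 SD rest on an assumed ρ of 0.7 and a realised imbalance of 0.5 SD. Severity is minor: only the secondary, preliminary effects of a pilot are touched, and the feasibility, usability and safety criteria do not depend on these tests.

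**What to change.** - Delete the sentence on baseline tests in Quantitative Analysis.
- Report baseline descriptively by randomised GSU arm, with the non-randomised Tübingen participants in a separate column and no P values.
- For the between-group effect on each secondary outcome, prespecify adjustment for its t0 value, for example ANCOVA of the t1 value on group and t0 value, and do not let baseline tests guide the choice of covariates.

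The cost is one deleted sentence, one added sentence and one degree of freedom per model. The t0 values are already collected and the sample size is unchanged. There is also a gain in precision. At ρ = 0.7 the outcome variance, relative to a t1-only comparison, is about 1 − 0.7² = 0.51 with adjustment, against 2 × (1 − 0.7) = 0.60 for change.

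### The between-arm analyses of the secondary outcomes leave out lesion level and completeness, the two stratification factors, so some of the tests are conservative if those factors predict outcome level

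*Protocol article*

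**What the plan says.** **Allocation.** The Randomization section states: "Only the 30 participants recruited at the GSU will be block randomized", and the blocks are "stratified by the level (high vs low paraplegia) and completeness (complete vs incomplete paraplegia) of the SCI with a block size of 4". That makes 2 × 2 = 4 strata. The Study Design section gives the allocation "with an allocation ratio of 1:1 for the intervention and waitlist control groups", so about 15 per arm.

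**Analysis.** Under Quantitative Analysis, "normally distributed continuous variables will be analyzed using a mixed analysis of variance model to test for significant effects for group and time". For skewed variables, "Wilcoxon and Mann-Whitney *U* tests will be conducted to test the differences between the groups and between t_0_ and t_1". The threshold is fixed: "The significance level will be set at *P*<.05".

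**Later use of the factors.** Lesion level returns once, as an option: "Subgroup analyses might be conducted for lesion level (high vs low paraplegia) and age". Completeness is not mentioned in that section. Table 1 and the Randomization section show that both factors are known for every randomised participant by the time of allocation.

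**The concern.** Stratified blocks force the arms to be similar on lesion level and completeness, so differences between strata contribute little to the chance difference between arms. A test that ignores the strata still puts that variance in its error term. If the strata are related to the outcome, the standard error is then larger than the true sampling variation, P values tend to be too large, and power is lost.

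At stake are peak exercise capacity, handgrip strength, SCIM III and SF-36 in a comparison of about 15 against 15. A conservative test at that size makes it easier to miss a signal that could inform the larger trials foreseen in Conclusions and Implications. Because the protocol names the model effects, the fallback tests and the significance level, the point is about a stated choice and not about detail left to a fuller plan.

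**Working it through.** **Inputs from the protocol.** 30 randomised, 1:1, four strata, blocks of 4, significance level 0.05. There is no power calculation to reproduce: the Sample Size section rests on earlier studies and usability recommendations, without an effect size, SD or power.

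**Assumptions, not in the protocol.** Two-sided tests; R², the share of outcome variance explained by level and completeness; a true difference of d = 0.8 SD; four equally common strata; a t0–t1 correlation of 0.7.

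**1. Type I error of an unadjusted comparison at t1.** With strata balanced between arms, the true variance of the mean difference is (1 − R²) times what the unadjusted test assumes. The nominal critical value t(28) = 2.048 then acts like 2.048/√(1 − R²):

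- R² = 0.10: 2.048/√0.90 = 2.159, two-sided tail area 4.0%
- R² = 0.25: 2.048/√0.75 = 2.365, tail area 2.5%
- R² = 0.40: 2.048/√0.60 = 2.644, tail area 1.3%

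Simulation with the actual blocks of 4 within strata (8,000 runs per scenario), which allows for incomplete blocks, agrees:

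| R² | Mann-Whitney at t1 | ANOVA group main effect |
|---|---|---|
| 0.10 | 3.9% | 4.0% |
| 0.25 | 2.5% | 2.5% |
| 0.40 | 1.1% | 1.2% |

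A second simulation (4,000 runs, correlation 0.7 within stratum) gives 4.4%, 2.5% and 0.9% for Mann-Whitney at R² = 0.10, 0.30 and 0.50. Linear models with the two factors added stay at 4.7% to 5.7% throughout.

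**2. Power at t1, d = 0.8.** Unadjusted: noncentrality 0.8 × √(15/2) = 2.19 on 28 df, power 56%. Adjusted: noncentrality 2.19/√(1 − R²) on 26 df.

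- R² = 0: 2.19, power 56%
- R² = 0.10: 2.31, power 60%
- R² = 0.25: 2.53, power 68%
- R² = 0.40: 2.83, power 78%

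By simulation, Mann-Whitney against the adjusted linear model gives 52% against 60% at R² = 0.10, and 53% against 71% at R² = 0.30.

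**3. Group-by-time interaction.** With two groups and two time points this equals a t test on the change score, so stable differences between strata cancel. From the second simulation (power at d = 0.8, strata explaining 30% of level):

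| Share of change explained by strata | Type I error, unadjusted | Power, unadjusted | Power, adjusted |
|---|---|---|---|
| 0% | 4.8–5.4% | 91.5% | 91.1% |
| 10% | 3.6–4.3% | 88.5% | 89.9% |
| 30% | 2.1–2.5% | 81.6% | 90.6% |

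**4. With the baseline value in the model.** When the strata do not predict change, adding them to a model of the t1 value that adjusts for baseline moves power from 86.1% to 85.6% (R² of level 0.10) or from 93.4% to 93.8% (0.30). Baseline adjustment has then already captured most of what the strata carry. If the strata explain 10% of change (R² of level 0.30), the move is from 88.9% to 92.9%.

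**The case against.** The strongest reply is that the treatment effect in a two-by-two mixed ANOVA is the group-by-time interaction, and step 3 shows that it neither gains nor loses unless the strata predict change over six weeks. The protocol does not say that they do. This stands, and it limits the point. It does not remove it, because the protocol names effects of group and of time, not the interaction, and it prescribes Mann-Whitney tests between groups.

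The group main effect is also a weak test of treatment in any case, because it averages in the baseline value: its simulated power at d = 0.8 is 20% or less, whatever the strata do. That is a reason to model the t1 value rather than only to add factors to the ANOVA.

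Naming the effects to be tested does not prove that the model holds nothing else, and a fuller plan might list covariates. That is possible for the ANOVA. It does not help the Mann-Whitney test, which has no place for them.

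A reader might go further and infer that the stated 5% level is simply untrue, or that every effectiveness result loses precision. The documents do not support this. They never say how prognostic level and completeness are; if they are not prognostic, nothing is lost. Nor does the mismatch make false positive findings more likely: the error runs only towards larger P values.

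**Conclusion.** The omission is plain on the text: the two factors that restrict the randomisation are not named in any stated between-arm analysis. Its consequence is conditional. If the strata explain 10% to 40% of the variance in outcome level, the Mann-Whitney test at t1 and the ANOVA group main effect run at about 4% down to 1% instead of 5%. Under the same assumption, a t1 comparison at d = 0.8 has 56% power unadjusted and 60% to 78% adjusted. The interaction is affected only if the strata predict change. These sizes rest on assumed values of R², d and the t0–t1 correlation.

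The outcomes are secondary, in a pilot with no powered hypothesis, and the Strengths and Limitations section already concedes limited conclusiveness. The feasibility, usability and safety criteria do not depend on these tests. This is a minor improvement that is nearly free, not a threat to the trial's conclusions. It concerns only the 30 randomised participants.

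**What to change.** In Quantitative Analysis, for the 30 participants randomised at the GSU:

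- Include lesion level (high or low) and completeness (complete or incomplete) as two main effects in the between-arm models, without stratum-by-group terms. Preferably model the t1 value with the baseline value as a covariate.
- For skewed outcomes, replace the unstratified Mann-Whitney test with a rank-based model containing the same two factors. A van Elteren test is an alternative, but strata average 30/4 = 7.5 people and may be too sparse for it, more so after dropout.

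**Cost.** One or two sentences, 2 of 28 degrees of freedom, and no new data. The downside is a power change of about 0 to 2 points at worst, if the strata are not prognostic or dropout is high. For example, with about 23 analysed (75% retention of 30 is 22.5), adding the factors to a change analysis lowered simulated power from about 77% to 75% when the strata did not predict change.

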### Aims of the Study

The primary aims of this trial are as follows:

To qualitatively assess the feasibility of an app-based exercise program (ParaGym) tailored by an algorithm to the needs of people with paraplegiaTo investigate the usability of the ParaGym app prototype in terms of the app’s design, information provided by the app, app’s ease of use, satisfaction with the app, and app’s functionality using the System Usability Scale (SUS)To assess the safety of this program by considering adverse events (AEs) and serious AEs (SAEs)

The secondary aim is to analyze the effects of a 6-week training intervention using the ParaGym mobile exercise app on peak exercise capacity, handgrip strength, independence, and health-related quality of life.

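### The plan names group and time as the ANOVA effects to test, but does not designate the group-by-time interaction or a baseline-adjusted t1 difference as the app's effect

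*Protocol article*

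**What the plan says.** The Aims of the Study section sets the question: "The secondary aim is to analyze the effects of a 6-week training intervention using the ParaGym mobile exercise app" on exercise capacity, grip strength, independence and quality of life. The Study Design section fixes two measurement times, t0 and t1, and describes the trial as randomized "with an allocation ratio of 1:1 for the intervention and waitlist control groups". The Randomization section limits this to one site ("Only the 30 participants recruited at the GSU will be block randomized") and adds that "The randomization code will be released after the participant has completed all baseline measures".

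The Quantitative Analysis section gives two routes, depending on distribution. Normally distributed outcomes "will be analyzed using a mixed analysis of variance model to test for significant effects for group and time". For skewed outcomes, Wilcoxon and Mann-Whitney "tests will be conducted to test the differences between the groups and between" the two visits. No section mentions a group-by-time interaction, a between-arm comparison of change, or a t1 comparison adjusted for the t0 value.

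**The concern.** Allocation is released only after baseline, so the app can act only on the t1 values of the intervention arm, and any difference between the randomized arms at t0 is chance. In that layout the app's effect is the difference in change between arms (the interaction) or the t1 difference given t0 (ANCOVA). Neither of the two effects named in the plan is that quantity.

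The article presents these results as preliminary insight into effectiveness, to be considered when future trials are planned. A diluted group effect could hide a real difference. A pooled time effect could be taken for benefit when both arms improved for reasons unrelated to the app. The Strengths and Limitations section itself warns that unrestricted additional sport may strongly affect the post-intervention measurements, so change in both arms is plausible.

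**Working it through.** The plan gives no power, effect size, SD or correlation for these outcomes, so there is no figure of its own to reproduce.

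**From the document:** 30 randomized, 1:1, so n = 15 per arm; significance level 0.05 (taken as two-sided).

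**Assumed:** unit SD at both visits; app effect d (in SD) present only at t1 in the app arm; t0-t1 correlation r of 0.5, 0.7 and 0.9; no dropout.

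**What each effect estimates.** Let D0 and D1 be the arm differences at t0 and t1.
- Group main effect: (D0 + D1)/2. Its expectation is (0 + d)/2 = d/2, and any chance D0 enters with weight one half.
- Interaction: D1 − D0, with expectation d.
- ANCOVA: D1 adjusted for t0, with expectation d.
- Time main effect: mean change over both arms. With no app effect and a shared gain g, its expectation is g.

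**Standard errors**, using 2/n = 2/15 = 0.1333:
- Group: √[0.1333 × (1 + r)/2], 28 df
- Interaction: √[0.1333 × 2(1 − r)], 28 df
- ANCOVA: √[0.1333 × (1 − r²)], 27 df
- t1 only: √0.1333 = 0.365, 28 df
- Time: √[2(1 − r)/30], 28 df

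Power comes from the noncentral t distribution with noncentrality equal to estimand divided by standard error. Worked case, d = 0.5 and r = 0.5: group 0.25/0.316 = 0.79, power 12%; interaction 0.5/0.365 = 1.37, power 26%; ANCOVA 0.5/0.316 = 1.58, power 33%.

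| True d | Test | r = 0.5 | r = 0.7 | r = 0.9 |
|---|---|---|---|---|
| 0.5 | Group main effect | 12% | 11% | 10% |
| 0.5 | Interaction | 26% | 40% | 84% |
| 0.5 | ANCOVA | 33% | 46% | 86% |
| 0.5 | t1 difference, unadjusted | 26% | 26% | 26% |
| 0.8 | Group main effect | 23% | 21% | 19% |
| 0.8 | Interaction | 56% | 78% | 99.7% |
| 0.8 | ANCOVA | 68% | 84% | 99.8% |
| 0.8 | t1 difference, unadjusted | 56% | 56% | 56% |

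The unadjusted t1 rows use a t test as a normal-theory stand-in for Mann-Whitney at t1.

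**Time effect with no app effect and a shared gain of 0.2 SD:** the noncentrality is 0.2/0.183 = 1.10, 0.2/0.141 = 1.41 and 0.2/0.082 = 2.45 for r = 0.5, 0.7 and 0.9. The test is significant in 18%, 28% and 66% of trials.

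**Simulation check** (20,000 trials, r = 0.7). With d = 0.8, the group effect rejected in 20.7% and the interaction in 78.1%. With no app effect and a shared gain of 0.3 SD, the time effect rejected in 53.7%, the interaction in 5.1% and the group effect in 5.0%.

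**The case against.** The strongest reply is that the phrase is shorthand. The article does not say main effects, and it does not say that either effect will be read as the effect of the app. A mixed ANOVA with one between-subject and one within-subject factor ordinarily includes the interaction, which is a usual reason for choosing it. That stands as far as it goes: a reader might infer that the investigators will report a main effect as the app's effect, and the text does not establish this. What remains is that three p-values are available and the article does not say which one answers the aim, while the two effects it does name are the wrong ones.

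A reader might also infer that the rank-based route fails in the same way. It does not. Group comparisons at baseline are specified separately, and the sentence introducing the ANOVA is placed at t1, so the Mann-Whitney test is naturally a comparison at t1. Among randomized participants that test is valid and targets the full app effect. It only forgoes the precision that baseline would add. The Wilcoxon test is different, since it compares visits and not arms.

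Nor is false-positive inflation in the group test a fair charge. Under randomization it keeps its 5% level, and its faults are a halved target and low power.

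Finally, the primary outcomes are feasibility, usability and safety. Their criteria (sessions completed, retention, the usability score and adverse events) do not use this model. The sample size rests on precedent, and the article already says the small sample limits conclusiveness. This limits how serious the point is, but does not remove it.

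**Conclusion.** The concern holds as one of designation. The plan names two effects that do not isolate the app and does not designate the one that would. If the wording is followed literally at 15 per arm, power for a 0.5 SD effect is 10-12% in place of 26-84% (interaction) or 33-86% (ANCOVA), and a shared 0.2 SD gain yields a significant time effect in 18-66% of trials. These ranges rest on assumed effect sizes, an assumed shared gain and correlations of 0.5 to 0.9, none of which the article gives. That the group main effect targets d/2, and that the time effect is not a between-arm contrast, follows from the design and needs no such assumption.

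For skewed outcomes the point is narrower: Mann-Whitney at t1 is acceptable but unadjusted, and Wilcoxon cannot show an app effect. The point should be fixed. It bears on the secondary outcomes of a pilot and leaves the primary criteria untouched.

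**What to change.** In the Quantitative Analysis section, state that:
- among the randomized participants, the app effect on each approximately normal secondary outcome is the between-arm difference at t1 adjusted for the t0 value (ANCOVA), reported with a 95% confidence interval; or, if the mixed ANOVA is kept, it is the group-by-time interaction;
- the group main effect, the time main effect and the within-group Wilcoxon tests are not interpreted as effects of the app;
- for skewed outcomes, the app effect rests on a between-arm comparison: Mann-Whitney at t1, or, where the t0-t1 correlation is high, Mann-Whitney on change scores or a rank-based ANCOVA.

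The restriction to randomized participants matters because the second site is not randomized. The cost is a few sentences of analysis wording. The t0 values are already collected, and no extra data are needed.
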